#### Reporting of SAEs (see ClinO, Art. 63)

The primary outcome and events on which the sample size is based represent postoperative complications which include SAEs. All SAEs within 90 days after surgery will be documented and analysed in this trial. As the origin of the SAEs is not intervention related, the SAEs are not actively reported to the EC in the applicable time limit of 15 days but are summarised in the annual safety report (ASR).

#### Notification of safety and protective measures (see ClinO, Art 62, b)

If immediate safety and protective measures must be taken during the conduct of the study, the investigator notifies the Ethics committee of these measures, and of the circumstances necessitating them, within 7 days.

### Frequency and plans for auditing trial conduct {23}

An annual safety report (ASR/DSUR) is submitted to the local Ethics Committee by the Investigator (ClinO, Art. 43 Abs) and will include postoperative complications described by the CCI within two unblinded safety analyses after 50 and 100 patients.

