### Outcomes {12}

The primary endpoint is the (CCI®) [9] within 90 days of surgery. The CCI is calculated as the sum of all Clavien–Dindo complications [17] (Additional file 1) that are weighted for their severity (multiplication of the median preference values from patients and physicians). The final formula yields a continuous scale that ranks the cumulative burden from any combination of complications from 0 to 100 in a single patient. As a composite complication score, the CCI has the advantage of reflecting the overall burden of the postoperative course that affects the health of patients and their quality of life. In addition, the CCI is a powerful endpoint in trials, as it allows sample size up to nine times lower compared with traditional morbidity endpoints [18]. Complications will be assessed from medical health records by an advanced nurse practitioner supported by a surgical resident and consultant, all of whom were already trained in the Clavien–Dindo classification in a pilot study. Outpatient information of complications treated at other institutions will be included.

Secondary endpoints are length and costs of hospital stay, readmission rates for inpatient hospital stay, smoking abstinence or nicotine reduction, nicotine dependence, mental health, quality of life, unplanned postoperative intermediate care or intensive care unit admissions and cost and. Secondary endpoints will be recorded up to a 12-month postoperative follow-up period and will be compared between the intervention and control group. Smoking abstinence or nicotine reduction will be assessed by measuring smoking status (cigarettes smoked per day) and nicotine dependence will be assessed using the Fagerström test [19]. Nicotine abstinence will be additionally confirmed by using the NicAlert cotinine saliva test. Quality of life will be assessed with the German version of the 36-Item Short Form Survey (SF-36; index values range from 0 to 1, with higher scores indicating better quality of life) including covering physical functioning, bodily pain, role limitations due to physical health problems, role limitations due to personal or emotional problems, emotional well-being, social functioning, energy/fatigue, and general health perceptions during the past 4 weeks [20]. Mental health will be assessed using the Hospital anxiety and depression scale (HADS) [21].

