### Procedure for unblinding if needed {17b}

Unblinding for the primary outcome will not be necessary.

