### Interim analyses {21b}

A blinded restricted re-evaluation of the standard deviation assumed for the sample size calculation will be performed after an information rate (IR) of 40% is reached, meaning that 40% of the patients have completed the 90-day follow-up assessment of the primary outcome CCI. The estimation of the standard deviation will be performed on the combined set of patients of the intervention and control group, and therefore unblinding is not necessary. If the standard deviation at interim is larger than anticipated, an increase of the sample size will be discussed. No reduction of the sample size is planned. No statistical reasons for stopping the trial at interim have been specified. The trial may be stopped for other reasons, including slower recruitment than anticipated.

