### Composition of the data monitoring committee, its role and reporting structure {21a}

The data monitoring committee (DMC) will reassess the data in a blinded fashion as described to check the variability to reassess the sample size calculation.

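### Two unblinded summaries of the primary endpoint, after 50 and 100 patients, pass through the investigator; the interim section does not list them, and they undermine the blinded sample-size review at about 90 to 100 patients

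*Protocol article*

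**What the plan says.** All references are to the protocol article.

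- **Frequency and plans for auditing trial conduct {23}.** The annual safety report "is submitted to the local Ethics Committee by the Investigator" and "will include postoperative complications described by the CCI within two unblinded safety analyses after 50 and 100 patients".
- **Outcomes {12}.** The primary endpoint is the CCI "within 90 days of surgery. The CCI is calculated as the sum of all Clavien–Dindo complications", so the safety summaries use the same measure as the primary analysis.
- **Interim analyses {21b}.** One look is listed: a check of the standard deviation once "40% of the patients have completed the 90-day follow-up assessment of the primary outcome CCI". It is made "on the combined set of patients of the intervention and control group, and therefore unblinding is not necessary". Then: "If the standard deviation at interim is larger than anticipated, an increase of the sample size will be discussed". The section rules out a reduction, names no statistical ground for stopping, and leaves stopping open for other reasons such as slow recruitment.
- **Composition of the data monitoring committee {21a}.** The DMC "will reassess the data in a blinded fashion" to check variability.
- **Procedure for unblinding if needed {17b}.** "Unblinding for the primary outcome will not be necessary".
- **Composition of the coordinating centre and trial steering committee {5d}.** The steering committee has two roles, the principal investigator and the statistical head. The principal investigator also meets weekly with the advanced nurse practitioner. Under Outcomes {12}, an advanced nurse practitioner assesses complications.

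**The concern.** A sample-size review on a pooled standard deviation protects the type I error because those who use it do not know the treatment difference. Here the investigator, presumably the principal investigator in this single-centre trial and hence half of the steering committee, would submit a document showing the primary endpoint unblinded shortly before or about when that review takes place. The review leads to a discretionary decision, and the article does not say who takes it.

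Two things are at stake. A decision to enlarge or stop the trial could be coloured by the emerging result. Knowledge of that result could also reach staff who counsel patients or grade complications. That matters because patients and counsellors know the allocation, and the only blinding described is outcome assessment from deidentified reports.

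**Working it through.** **1. The plan's own sample size.** Inputs from Sample size {14}: means 13 and 5.5 (difference 7.5), SD 20, two-sided 5%, power 80%.

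- Normal approximation: n per arm = 2 × (1.96 + 0.8416)² × 20² / 7.5² = 111.6, so 112 per arm and 224 in total.
- Two-sample t-test: 112.6, so 113 per arm and **226** in total, as stated.
- Dropout: 226 / 0.9 = 251.1, matching the stated **251**.

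**2. When the looks fall relative to the review.**

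- 40% of 226 = 90.4; 40% of 251 = 100.4. The article does not say which total is the base.
- Look at 50: 50/226 = 22% or 50/251 = 20% of information, before the review on either base.
- Look at 100: 100/226 = 44% or 100/251 = 40%, at or just after the review.

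**3. How much the looks reveal.** SE of the difference with equal arms = 20 × √(4/n).

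| Patients | SE | Expected z if the true difference is 7.5 | Chance of p < 0.05 |
|---|---|---|---|
| 50 | 5.66 | 7.5/5.66 = 1.33 | 26% |
| 100 | 4.00 | 7.5/4.00 = 1.88 | 47% |

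This assumes that every counted patient has a complete 90-day CCI. The auditing section does not say whether patients means randomised, operated or followed up; with fewer complete records the looks say less.

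**4. Effect on type I error, under three uses of the looks.**

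- *Neither tested nor acted on:* 5%.
- *Each look tested at two-sided 5% and able to end the trial, plus the final test* (2 million simulated null trials, unadjusted limit 1.96): 11.5% with final N = 226 and 11.7% with 251.
- *N raised after seeing the by-arm result at 100 patients, chosen to do the most harm, final test unadjusted.* For each interim z₁ the conditional error is 1 − Φ[(1.96 − z₁√t)/√(1 − t)], with t = 100/N; it is maximised over the allowed N and averaged over z₁. The caps are assumptions, since the article gives none.

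| Assumed cap | One-sided error (nominal 2.5%) | Two-sided, doubled |
|---|---|---|
| 1.25 × N | 2.7% | 5.4% |
| 1.5 × N | 2.8 to 2.9% | 5.6 to 5.7% |
| 2 × N | 3.0 to 3.1% | 6.0 to 6.1% |

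**5. The sections side by side.** The interim section needs no unblinding for its one look, the DMC's role is blinded, and the unblinding section sees no need to unblind the primary outcome. The auditing section schedules two unblinded summaries of that outcome. Data management {19} has the de-identified study report generated at the end of the study, and Data Availability starts statistical programming once the database is final, so neither provides for the two earlier analyses.

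**The case against.** The case on the other side is substantial.

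- **The looks are planned.** Their number and timing are fixed in advance and they are called safety analyses. In this trial safety and efficacy share a measure: the SAE section says that the primary outcome, postoperative complications, includes SAEs. A reader might infer unplanned efficacy looks; the text does not support that. What is missing is their mention in the interim section and a statement that nothing follows from them.
- **The SD review stays pooled.** It is computed on both arms combined, assigned to the DMC, and can only lead upwards. Knowing the arm means does not change the pooled SD. A reader might infer that the review is defeated; that goes too far.
- **The conflicting statements are narrower than they look.** The interim sentence concerns the SD estimate, the DMC sentence the variability check, and the unblinding sentence answers a heading about procedure. None says that safety reporting is blinded. This makes them hard to square with the auditing section rather than flatly contradictory to it.
- **The chain of access is not written down.** No decision-maker is named, nothing sends the report to counsellors or assessors, and the article says who submits it, not who prepares it. By arm is the natural meaning of unblinded but is not spelled out. Influence is possible, not shown.
- **The full protocol and SAP were not available for this review**, and may set out access and the re-estimation rule.

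All of this limits the size of the point. It does not remove it: the article itself routes unblinded primary-endpoint data through the investigator, and that is a stated arrangement, not a detail left to another document.

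**Conclusion.** The point holds in a limited form. As written, the investigator would hold an unblinded summary of the primary endpoint before the blinded sample-size review and a second one at about the time of it. The interim section does not acknowledge these looks, and the choice they could influence is discretionary. This undermines the blinded review without by itself defeating it.

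The plan's type I error should not be reported as 11.5% or 6%. The first figure needs a test at each look and a right to stop on it; the article plans no such test and names no statistical stopping reason. The second needs N to be picked from by-arm data in the most damaging way under an assumed cap of twice N, whereas the article ties any increase to the SD. Both bound what misuse could do. If the looks are neither tested nor acted on, the error rate is 5%. The risk of changed behaviour once the difference is known cannot be quantified from the article.

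**What to change.** 1. **Auditing section {23}.** In the investigator's annual report, give complications and the CCI pooled over arms. If by-arm safety data are wanted, put them in a closed report to the ethics committee, prepared and sent by someone outside the trial team and withheld from the investigator, steering committee, counsellors and CCI assessors. Send it to the DMC as well only if the rule in item 3 is mechanical, because the DMC carries out the blinded review. Define what 50 and 100 patients count.
2. **Interim section {21b}.** List the two looks, and state that no efficacy test and no decision on sample size or stopping follows from them. Bring the unblinding {17b} and DMC {21a} sections into line.
3. **Sample-size rule.** Replace the open discussion with a fixed rule on the pooled SD, for example N = 226 × (SD/20)², never below 226, with a stated cap, applied without by-arm data. The pooled SD contains part of any treatment effect: under the plan's own assumptions it is √(400 + 7.5²/4) = 20.35, giving 226 × 414.06/400 = 234. That is 8 evaluable patients more, a small price for keeping the review blinded.

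The cost is mainly wording in the protocol and SAP, plus a separate preparer if a closed report is kept. The downside is that the investigator's report no longer shows the CCI by arm. The change should be in place before the first look, because disclosure cannot be undone.

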### Plans for communicating important protocol amendments to relevant parties (e.g. trial participants, ethical committees) {25}

Substantial changes to the study setup and study organization, the protocol and relevant study documents are submitted to the Ethics Committee for approval before implementation. Under emergency circumstances, deviations from the protocol to protect the rights, safety and well-being of human subjects may proceed without prior approval of the Ethics Committee. Such deviations shall be documented and reported to the Ethics Committee as soon as possible.

Substantial amendments are changes that affect the safety, health, rights and obligations of participants, changes in the protocol that affect study objectives or central research topic, changes of study site or of study leader and sponsor (ClinO, Art. 29).

A list of all non-substantial amendments will be submitted to the competent EC together with the ASR.

### Dissemination plans {31a}

Publications in peer-reviewed journals are planned.

## Discussion

The dedicated smoking cessation intervention is expected to cause sustained abstinence from smoking in a large percentage of the patients. The hypothesis is that the preoperative smoking cessation program improves outcomes in smokers undergoing surgery. The study will reveal if the expectations on successful smoking cessation rates are reasonable.

To date, only two RCTs have investigated the effects of an intensive preoperative smoking cessation program on postoperative complications [5, 6]. Even though the preoperative period is considered as a window of opportunity for cessation counselling randomized controlled evidence regarding its efficacy is still lacking. A systematic Cochrane Review showed evidence for increased short-term smoking abstinence in patients undergoing preoperative cessation counselling, whereas the effects on long-term abstinence and postoperative morbidity remained unclear [7].

In contrast to these previous studies, postoperative morbidity will be assessed using the CCI over a 90-day period. The CCI has been proven to be a strong endpoint, as it reflects the overall burden of the postoperative course in a single patient and thus allows for smaller sample sizes compared with traditional morbidity endpoints.

In line with most RCTs regarding preoperative cessation counselling, it is likely that the major limitations of our trial will be the relatively short preoperative period and the intensity of cessation counselling. To overcome these barriers our trial will only enrol patients who are scheduled for surgery with a preoperative period of more than one month and an intensive cessation program consisting of weekly behavioural support and pharmacotherapy will be implemented in as many patients as possible.

### Trial status

Recruitment will be started in June 2022 with the completion of recruitment in 2025.

## Data Availability

[name] will have access to the final trial dataset. Statistical programming will be initiated upon finalization of the data base. The deidentified dataset will be provided to the trial statistician for analysis.

## Abbreviations

AE: Adverse event
ASA: American Society of Anaesthesiologists
ASR/DSUR: Annual Safety Report/Development Safety Report
BASEC: Business Administration System for Ethical Committees
CCI: Comprehensive Complication Index
CCM: Chronic Care Model
ClinO: Ordinance on Clinical Trials in Human Research (in German: KlinV, in French: OClin, in Italian: OSRUm)
CRF: Case Report Form
CTCAE: Common Terminology Criteria for Adverse Events
FAS: Full analysis set
eCRF: Electronic Case Report Form
FOPH: Federal Office of Public Health
GCP: Good Clinical Practice
HADS: Hospital anxiety and depression scale
HRA: Human Research Act (in German: HFG, in French: LRH, in Italian: LRUm)
ICH: International Conference on Harmonisation
ITT: Intention to treat
SAE: Serious adverse event
SF-36: 36-Item Short Form Survey
TTS: Tobacco treatment specialist
TTM: Transtheoretical Model
